### Sample size and power calculation

The results of previous clinical trials showed that around 70% of the active dentine caries became arrested after 30 months [18]. The anticipated caries-arresting rates of group B would be 80%. An absolute difference of 10% for the caries-arresting rates between treatment groups is considered to be clinically significant. The sample size calculation is based on the expected proportion of caries that become arrested, with the power of the study set at 90% (*β* = 0.1) and a two-sided 95% confidence interval (*α* = 0.05) as the statistical significance level by using the G*Power Version 3.1.9.2 (Franz Faul, Universität Kiel, Germany). Therefore, at least 820 active carious tooth surfaces need to be included, or 410 in each study group. Based on the results of epidemiological surveys, we anticipate that the mean number of active caries tooth surfaces of 3-year-old children in Hong Kong is approximately three [25]. The intraclass correlation coefficient for dental caries data at the surface level within the individual would be approximately 0.13 [26]. Following the equation for the required sample size in a multilevel study [27], the design effect will be 1.26. Thus, the estimated sample size would be at least 346 children, or 173 per group. The anticipated dropout rate is 15% [24]; thus, 408 children (204 children in each group) will be needed at baseline.

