### Randomization, treatment allocation and allocation concealment

Participating children with dental caries will be categorized into two strata by the number of carious surfaces they have (one to three or more than three tooth surfaces). The children will be then allocated by a stratified randomization method with a block size of 6 into two groups. The allocation sequence will be generated by a technician who will not be involved in the oral examination and patient allocation. A pile of sealed opaque envelopes with the allocation numbers will be prepared. Those envelopes will be held by a dental assistant in the field. The assistant will know the treatment allocation only when they open the envelope.

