### Surface-level analysis

Because more than one carious lesion may be included from one child, these lesions will possibly be correlated or clustered. Therefore, an adjustment of the clustering effect will be required. Multilevel logistic regression analysis will be adopted to assess the relative effectiveness of a 25% AgNO_3_ and a 5% NaF varnish with or without fTCP in arresting dentine caries. A two-level model will be used: level 1, tooth surface level, and level 2, subject level. Multilevel logistic regression models with a clustering effect adjustment will be performed to analyze the effect of independent variables on the caries-arresting outcomes at the 12-, 18- and 30-month follow-ups. Besides treatment group assignment, other potential variables, such as demographic characteristics (sex and age), oral hygiene status, oral-health-related behaviors, level of parental education, family income, caries condition (baseline dmfs scores, tooth position, lesion site and presence of plaque on lesion), also will be included in the model as covariates.

The secondary outcome (preventive effect) is the mean of caries increment at the 6-, 12-, 18-, 24- and 30-month examinations. A paired *t* test will be performed to assess the difference in the caries increment between the two groups at all follow-up examinations. Multilevel generalized linear models will be adopted to assess the effect of independent variables on the caries increment between two groups at 12, 18 and 30 months.

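### The plan calls a 10-point absolute difference in arrest clinically significant, but its stated model yields an odds ratio and no cluster-adjusted difference with an interval is stated

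*Protocol article*

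**What the plan says.** The Outcome measure section defines the primary outcome as a proportion: the share of initially active carious surfaces that have become arrested.

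The Sample size and power calculation section plans on the same scale. Earlier trials are cited for "around 70% of the active dentine caries became arrested after 30 months", and for the new varnish "The anticipated caries-arresting rates of group B would be 80" per cent. It then states: "An absolute difference of 10% for the caries-arresting rates between treatment groups is considered to be clinically significant". Power is 90% and the test is two-sided at 0.05, giving "at least 820 active carious tooth surfaces need to be included, or 410 in each study group".

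For the comparison of arrest between groups, the Surface-level analysis section says: "Multilevel logistic regression analysis will be adopted to assess the relative effectiveness". The model has two levels, surface and child, and is fitted at 12, 18 and 30 months with a list of covariates. The list is open-ended and includes baseline dmfs. No effect measure is named: neither an odds ratio nor a difference in proportions.

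On allocation, the Randomization section says: "The children will be then allocated by a stratified randomization method with a block size of 6 into two groups". The two strata are one to three carious surfaces and more than three. This factor is not named among the model covariates.

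**The concern.** The treatment coefficient of a two-level logistic model is a log odds ratio, conditional on the child's random effect and on the covariates. The article's statement of what matters clinically is a difference in proportions. The two are linked only through the control arrest rate and, to a lesser degree, the between-child variance. A reader given an odds ratio and its interval could reject or retain the null hypothesis, but could not tell from those figures whether the interval includes or excludes 10 points. If the scale of the headline result is left open, it could also be chosen after the results are known.

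The stratum is a separate and smaller matter. When randomisation is stratified, the analysis normally carries the stratification factor, so that the standard error matches the design. This has no bearing on the scale of the result.

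**Working it through.** **1. The plan's own sample size.** Inputs from Sample size and power calculation: 0.70 and 0.80, two-sided 0.05, power 90%, three active surfaces per child, ICC 0.13, 15% dropout.

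- Two proportions, pooled variance under the null: n = [1.960 × √(2 × 0.75 × 0.25) + 1.282 × √(0.21 + 0.16)]² / 0.10² = 392 per group. With continuity correction it is 412, against 410 stated.
- Design effect: 1 + (3 − 1) × 0.13 = 1.26, as stated.
- Children: 820 × 1.26 / 3 = 344.4. From 824 surfaces (2 × 412) it is 346.1, against 346 stated.
- Dropout: 173 / 0.85 = 203.5, so 204 per group and 408 in all, as stated.

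The sizing reproduces, and it rests on a difference in proportions throughout.

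**2. The design effect on other scales.**

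- Risk ratio: 0.80 / 0.70 = 1.14.
- Population (marginal) odds ratio: (0.80/0.20) / (0.70/0.30) = 1.71.
- Child-specific odds ratio: take a random intercept with SD σ. Find a and b such that the average of expit(a + σZ) is 0.70 and the average of expit(b + σZ) is 0.80, with Z standard normal (Gauss–Hermite integration). The odds ratio is exp(b − a).

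The article does not say on which scale the ICC of 0.13 is measured, so both readings are shown:

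| ICC 0.13 read as | Variance of intercept | SD | Child-specific OR |
|---|---|---|---|
| latent: 0.13/0.87 × π²/3 | 0.492 | 0.70 | 1.80 |
| observed scale, matched at 75% arrest | 0.855 | 0.92 | 1.86 |

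These figures leave the other covariates out.

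**3. Cost of confusing the two kinds of odds ratio.** Suppose the child-specific value is taken for a population one at 70% control arrest. The odds are 1.797 × 7/3 = 4.194, so the proportion is 4.194/5.194 = 0.807, an apparent gain of 10.7 points. With 1.857 it is 11.2 points. The true gain is 10, so the error is about one point.

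**4. What a fixed odds ratio means in points.** Hold each odds ratio at its value for 70% versus 80% and vary the control rate. The control rates other than 70% are assumptions for illustration.

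| Control arrest | Child-specific 1.80 | Child-specific 1.86 | Population 1.71 |
|---|---|---|---|
| 50% | 12.9 | 12.8 | 13.2 |
| 60% | 11.9 | 11.8 | 12.0 |
| 70% | 10.0 | 10.0 | 10.0 |
| 80% | 7.4 | 7.4 | 7.3 |
| 85% | 5.8 | 5.9 | 5.7 |

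The columns nearly agree. The spread therefore comes from using a ratio scale when the control rate is not fixed, and hardly at all from the conditional nature of the model.

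**5. The stratum.** The strata are cut on the number of carious surfaces. The decayed part of dmfs counts carious surfaces, and baseline dmfs is a listed covariate. Much of the stratum's information is therefore already in the model, though not the factor itself.

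**The case against.** The strongest reply is that nothing here is an error. The stated hypothesis is one of no difference, and the model's treatment coefficient tests it. Planning on two proportions and analysing with a cluster-adjusted logistic model is ordinary practice. The 10 points appear only in the sample size section, and no sentence says that the final interval will be judged against them. How an effect is expressed is often settled in an analysis plan, which is not at hand. This stands as far as it goes: the test is not in question, and the point concerns how the result is expressed. But the article itself fixed both the threshold and the model, and the two are on different scales.

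A reader might infer that the model can give only an odds ratio, or that the result cannot be read against the threshold at all. The documents do not support either. No effect measure is named. The primary outcome is a proportion, so group proportions are its natural summary. A fitted multilevel logistic model can also be averaged over children and covariates to give proportions and their difference. The Subject-level analysis section further says that the mean of the primary outcome will be treated as normal, which hints at a child-level comparison on the absolute scale. It names no between-group test or interval for arrest, however, so it does not settle the matter.

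It is also fair to say that the spread in points rests on hypothetical control rates. The trial will observe its own rate, and the article expects about 70%.

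On the stratum, the covariate list is open and already has baseline dmfs. Its omission from the list is no ground for doubting the result.

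**Conclusion.** The point holds in a limited form. The article's threshold is an absolute difference of 10 points, the coefficient of its stated model is a child-specific log odds ratio, and no cluster-adjusted absolute difference with an interval is stated. At the design values the gap between the child-specific odds ratio (1.80 to 1.86) and the population one (1.71) is small. The practical weakness is that an odds ratio reported alone shows whether 10 points was reached only if control arrest is near the planned 70%.

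The figures assume a normal random intercept, an ICC of 0.13 on one or the other scale, and no further covariates. Neither the sample size nor the validity of the test is affected. The missing stratum term is minor and independent of the scale question. The change is worth making before the analysis.

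**What to change.** Add to the analysis of the primary outcome, in substance: from the two-level logistic model at 30 months, the standardised (marginal) proportion of surfaces arrested will be reported for each group, with their difference and a 95% confidence interval that allows for clustering by child. This difference is the headline result and will be read against 10 percentage points. The odds ratio will be given as supporting, labelled as child-specific.

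The interval can come from a bootstrap that resamples whole children. If the marginal predictions are awkward to obtain in the chosen software, a GEE with the child as cluster would serve for the same purpose.

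Separately, name the randomisation stratum (one to three versus more than three carious surfaces) as a fixed effect. The gain is modest, because baseline dmfs already carries part of it.

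The cost is a few lines of text and one extra output from a model that will be fitted anyway. No new data are needed.

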### Statistical methods

The collected data will be entered into an Excel file by two persons separately, and the data will be proofread to minimize data-entry error. Data will be analyzed using the software SPSS 24.0 for Windows (SPSS Inc., Chicago, IL, USA). The statistical significance level for all tests will be set at 0.05.

An intra-examiner agreement in the diagnosis of dental caries will be assessed by Cohen’s Kappa statistics. An intention-to-treat analysis will be undertaken. The dropout rates of the two groups will be expected to be similar as the treatment protocols and treatment outcomes (arrested caries with blackening of the lesion) are similar.

### Subject-level analysis

A chi-square test and *t* test will be performed, as appropriate, to analyze the differences between the groups regarding the children’s demographic background, oral hygiene and baseline caries experience (dmfs score). A chi-square test will also be conducted to study the difference in dropout rates between groups during the follow-ups. A paired *t* test will be used to compare the changes in ECOHIS, while the McNemar test will be used to compare the changes in oral-health-related behaviors at baseline and follow-up examinations between the different groups. Although the distribution of data for the primary outcome may not be normal, making use of the central limit theorem with the relatively large sample size in this research, the distribution of the mean will be considered normal.

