## Methods/design

### Trial design

This is a double-blind, two-armed, parallel-design randomized controlled trial. The Standard Protocol Items: Recommendations for Interventional Trials (SPIRIT) 2013 Statement will be followed in this trial (Additional file 1) [23]. The schedule of this study is presented in Fig. 1.

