### Questionnaire survey

A parental questionnaire regarding each child’s oral hygiene, snacking habits, use of fluoride agents, dental-visit behavior, parental educational level and family monthly income will be administered at baseline and at 12-, 18- and 30-month follow-up visits. To assess the children’s oral-health-related quality of life, the translated and validated Chinese-language Early Childhood Oral Health Impact Scale (ECOHIS) will be adopted in the parental questionnaire. The questionnaires will also assess parental satisfaction with their child’s oral health and dental esthetics. In the follow-up questionnaire, parents of the study children will also be asked to report the post complications of assigned treatments, such as pain, from a treated tooth and gingival irritation around a treated tooth.

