## Discussion

This is a randomized, double-blind clinical trial aiming to investigate the caries-arresting effectiveness of the semi-annual application of a 25% AgNO_3_ solution followed by a 5% NaF varnish with/without fTCP among preschool children. The caries-preventive effect, parental satisfaction, changes in oral-health-related quality of life of the study children and the adverse effects of the two intervention groups also will be evaluated.

Due to the limitations of the study, the use of dental radiographs is unavailable and unsafe when conducting a trial in kindergartens [18, 24]. The visual-tactile inspection without x-rays will be adopted for assessing the lesion activity at baseline and follow-up examinations, which is similarly to other caries-arresting studies [28]. To generalize the research findings to general populations, the recruited children will not be asked to change their routine oral care practices including the use of fluoride toothpaste and tooth-brushing habits. Instead, the data of oral care practice habits will be collected by questionnaires and analyzed as confounding factors. The 30-month study period is optimal to investigate the effect of caries-arresting treatment in the long run. The follow-up examinations, which will be conducted every 6 months, will provide the trends or changes of lesion activities over 30 months after receiving the intervention. After finishing this study, all recruited children will be eligible to attend primary schools, and the decayed teeth can be restored by School Dental Care Service which is provided by the Department of Health for primary school students in Hong Kong.

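### The McNemar test, and probably the paired t test for ECOHIS, is assigned to a between-arm comparison of change that a within-child test cannot make

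*Protocol article*

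**What the plan says.** The design is two independent groups. Under Trial design: "This is a double-blind, two-armed, parallel-design randomized controlled trial". Under Randomization, treatment allocation and allocation concealment: "The children will be then allocated by a stratified randomization method with a block size of 6 into two groups". The strata are defined by the number of carious surfaces, and nothing matches a child in one arm to a child in the other.

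Behaviours and ECOHIS come from the parental questionnaire, which "will be administered at baseline and at 12-, 18- and 30-month follow-up visits" (Questionnaire survey).

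The tests are named in one sentence under Subject-level analysis. Its first clause reads "A paired *t* test will be used to compare the changes in ECOHIS". Its second clause, joined by a contrast word, reads "the McNemar test will be used to compare the changes in oral-health-related behaviors at baseline and follow-up examinations between the different groups". The reference to groups stands in the second clause only.

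The Discussion adds that "changes in oral-health-related quality of life of the study children and the adverse effects of the two intervention groups also will be evaluated".

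**The concern.** A McNemar test or a paired t test needs pairs. In this trial the only pairs are one child's baseline and follow-up answers. Run on those pairs, either test asks whether a proportion or mean moved over time, within one arm or in the pooled sample. Neither asks whether it moved differently in group A and group B, which is the contrast the sentence states for behaviours.

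The distinction matters because the children are 3 to 4 years old at entry and are followed for 30 months. Change within an arm mixes growing up, new caries and treatment. Only the contrast between arms is protected by randomisation. A reader given a McNemar or paired t result as an arm comparison could be misled in two ways: a shared time trend could be taken for a treatment effect, or a real difference between arms could be missed.

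**Working it through.** **1. Does another named method cover the contrast?**

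| Section | Method | Applied to |
|---|---|---|
| Subject-level analysis | chi-square, t test | demographic background, oral hygiene, baseline dmfs; chi-square also for dropout |
| Subject-level analysis | paired t test | change in ECOHIS |
| Subject-level analysis | McNemar test | change in behaviours, between groups |
| Surface-level analysis | multilevel logistic regression | caries arrest; behaviours enter as covariates |
| Surface-level analysis | paired t test, multilevel generalized linear models | caries increment |

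No row compares change in behaviours or ECOHIS between arms by a method with a treatment term.

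**2. Is the ECOHIS clause meant between arms?** The wording leaves it open. Surface-level analysis offers support: "A paired *t* test will be performed to assess the difference in the caries increment between the two groups at all follow-up examinations". There too a paired test is assigned to two independent arms, so the same use for ECOHIS is plausible.

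**3. The plan's own sample size, used as the input n.** Design effect = 1 + (3 − 1) × 0.13 = 1.26. Children per arm = 410 × 1.26 / 3 = 172.2, rounded up to 173 (346 in all). With 15% dropout, 173 / 0.85 = 203.5, rounded up to 204 (408 in all). The plan's figures reproduce and are not in dispute. The article states no power for ECOHIS or behaviours.

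**4. Illustration: arms judged by separate paired t tests.** Assumptions: n = 173 per arm, two-sided α = 0.05, and the same true mean change in both arms, d, in SDs of the change score. The protocol gives no size for d, so a range is shown. Power within one arm, P, comes from the noncentral t distribution with 172 degrees of freedom and noncentrality d√173. The probability that exactly one arm is significant is 2P(1 − P).

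| d (SD of change) | d√173 | P | exactly one arm significant |
|---|---|---|---|
| 0 | 0 | 0.050 | 9.5% |
| 0.10 | 1.315 | 0.258 | 38% |
| 0.15 | 1.973 | 0.501 | 50% |
| 0.20 | 2.631 | 0.744 | 38% |
| 0.25 | 3.288 | 0.905 | 17% |
| 0.30 | 3.946 | 0.975 | 4.8% |
| 0.35 | 4.604 | 0.996 | 0.9% |
| 0.40 | 5.261 | 0.9995 | 0.1% |

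A valid between-arm test would reject in 5% in every row.

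**5. Illustration by simulation** (4,000 trials, 173 per arm; all changes assumed). The between-arm test here is a two-sample test on within-child change.

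| Truth | pooled within-child test rejects | exactly one arm significant | between-arm test rejects |
|---|---|---|---|
| ECOHIS, both arms change 0.2 SD | 95.5% | 37% | 5.4% |
| ECOHIS, +0.2 against −0.2 SD | 4.3% | 38% | 95.9% |
| Behaviour, both arms 20% gain and 10% lose it | 92.5% | 46% | 4.8% |
| Behaviour, 20%/10% against 10%/20% | 3.5% | 47% | 92.5% |

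The pooled within-child tests respond to change over time. They almost always reject when the arms do not differ, and almost never when the arms move in opposite directions.

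**The case against.** **ECOHIS.** The mention of groups closes only the McNemar clause, and a paired t test is valid for change in the same child. The Discussion gives weak support, because the phrase about the two intervention groups attaches most naturally to adverse effects. This stands: the between-arm reading for ECOHIS is likely, not certain. If only change over time is meant, the test is sound, and a between-arm ECOHIS method may simply have been left to a fuller document.

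**Behaviours.** The article treats these chiefly as confounders, says that routine oral care will not be altered, and states no hypothesis that the added ingredient changes them. This lowers the importance of the comparison. It does not make the McNemar test able to perform it, and the sentence does claim to compare groups.

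**Illustration.** The percentages depend on assumed changes, on the SD being that of the change score, and on a side-by-side reading of two p-values that the article does not state. Discordance peaks near 0.15 SD and is no higher than the 5% comparator from about 0.30 SD. All of this stands, so the figures show a mechanism and do not predict this trial's error rate.

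**A stronger reading.** A reader might infer that the between-arm comparisons will not be made at all, or that they will be made by setting two within-arm p-values side by side. The article supports neither. It intends a comparison between groups for behaviours and gives no decision rule, and the investigators may in practice use another test. What the text supports is that the tests named cannot make the comparison.

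**Conclusion.** For behaviours the mismatch is plain on the face of the text: a within-child test is assigned to a contrast between independent arms. For ECOHIS the same holds on the likely reading, and the intended contrast should be clarified. The conclusion needs only the parallel, unmatched design and the definition of the tests. The size does rest on assumptions: under separate paired tests and equal true change, spurious disagreement between arms ranges from 50% at its worst (0.15 SD of the change score) to 5% or less from 0.30 SD.

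The impact is modest. Neither ECOHIS nor behaviours is the primary or the named secondary outcome, and the multilevel logistic model for caries arrest includes treatment and is unaffected. The paired t test named for caries increment is the same error on a more important outcome, although multilevel generalized linear models also address that outcome at 12, 18 and 30 months. The correction is worth making because it costs so little.

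**What to change.** Say for each outcome whether change over time, a difference between arms, or both is intended. Where arms are compared:

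- **ECOHIS:** ANCOVA of the follow-up score on treatment, baseline score and randomisation stratum. A two-sample test on within-child change is a simpler valid alternative.
- **Binary behaviours:** logistic regression of follow-up status on treatment, baseline status and stratum.
- **Paired t and McNemar tests:** keep only to describe change over time within arms, and label them so.

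The cost is a change of analysis wording. The questionnaire already collects the variables at baseline and follow-up, the stratum is known from randomisation, and the sample size does not change.
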